#### Primary outcome

We use self-reported changes from baseline in the SDQ total difficulties score [32] by the pupils as the primary outcome. SDQ measures behavioural and emotional functioning and social competencies, which is highly relevant according to WHO´s definition of mental health e.g. the ability to manage thoughts, emotions, as well as to build social relationships [1]. SDQ is recommended as a measure of child well- being in community settings such as schools [33].

Our primary end-point is 6 months after baseline. Our primary study population is the vulnerable sub group with a SDQ total difficulties score above the 80th percentile [34]. They will be taught the “.b” programme together with the whole class as a part of compulsory class room teaching.

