### Sample size

Based on our pilot study, we expect a reduction of 1.5 score points (sd 3.8) in the SDQ total difficulties score among the vulnerable sub group. To detect this effect with a statistical power of 80%, it requires a study sample of 102 pupils in each group; 204 in total.

To detect a reduction of 0.7 score points (sd 5.5) in the SDQ-total difficulties score among the total pupil population, requires a study sample of 971 pupils in each group; 1942 in total.

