### Recruitment

From May 2018—May 2019, we recruited schools through letters to school headmasters, local information meetings and by advertising on our website (www.mindfulness.au.dk) and other social media (Facebook and Instagram). We informed the school headmasters and interested teachers that the schools would be randomised to begin teacher training in 2019 (intervention group) or in 2020 (control group). We further informed that it was an obligation for each teacher to recruit one 5–8 class with 15 to 28 pupils in a year from randomisation corresponding to the time of the completion of teacher training in the intervention group to test the effectiveness of the “.b”-programme. We recruited schools in five blocks defined by the five regions. We have included a total of 110 Danish schools and 191 teachers who consented to participate in the trial; 27 schools and 56 teachers from the Capital Region of Denmark, 18 schools and 28 teachers from Region Zealand, 25 schools and 42 teachers from Region of Southern Denmark, 30 schools and 50 teachers from Central Denmark Region and 10 schools and 15 teachers from North Denmark Region.

We expect teachers to recruit approx. 2000 pupils in total for the trial. We expect that approx. 400 pupils will be in the vulnerable sub group resulting in a SDQ total difficulties score > 80% percentile at baseline.

In this real-life setting, it was not possible to include the pupils before the randomisation of the schools due to the logistics of teacher planning.

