### Statistical methods

Data will be analysed by a repeated measurement model with the systematic effect: region, type of school, school size, sex (pupil), class, time (three time points), intervention, interaction between time and intervention, and random effect of school, teacher/class within school and pupil within class.

Confidence intervals and standard errors will be found by bootstrapping to adjust for possible deviation from normality of the random effects.

We will perform four sensitivity analyses representing scenarios with data not missing at random. In these sensitivity analyses, missing outcomes will be substituted with predictions based on the analysis models above adding or subtracting 0.2*SD in the intervention or control arm.

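### The planned pupil random intercept implies equal variances and correlations at all three visits, which cannot hold in a primary population selected on baseline SDQ; the 6-month effect is open to modest bias if loss depends on earlier scores differently by arm

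*Protocol article*

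**What the plan says.** The Statistical methods section gives one repeated-measures model. Its fixed effects include "time (three time points), intervention, interaction between time and intervention", so baseline is part of the outcome vector and the effect is read from the interaction. Dependence is carried by "random effect of school, teacher/class within school and pupil within class". No residual structure and no visit-specific variance is named.

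Under Primary outcome, the analysis set is fixed on the primary outcome's own baseline value: "Our primary study population is the vulnerable sub group with a SDQ total difficulties score above the 80th percentile". Recruitment confirms when the cut is taken and the expected size: "approx. 400 pupils will be in the vulnerable sub group resulting in a SDQ total difficulties score > 80% percentile at baseline". The time of interest is also set there: "Our primary end-point is 6 months after baseline".

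Standard errors and confidence intervals are to be bootstrapped. In the four sensitivity analyses, "missing outcomes will be substituted with predictions based on the analysis models above", shifted up or down by 0.2*SD in one arm or the other. The article states no expected loss to follow-up and no difference in loss between arms.

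**The concern.** A single pupil intercept plus independent residuals of constant variance is compound symmetry: one variance and one covariance for all three visits. Selecting pupils on a high baseline score truncates the baseline distribution and leaves the follow-up scores untruncated. The baseline variance must then be smaller than the follow-up variances, and the baseline-to-follow-up correlation lower than that between 3 and 6 months.

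This matters only through missing data. A likelihood analysis fills in lost pupils implicitly, by the regression of the missing score on the observed ones, and that regression comes from the fitted covariance. If the implied slope of the 6-month score on baseline is too flat, lost pupils with high baselines are placed too low and those with low baselines too high. The error cancels between arms if loss works alike in both, and remains if it does not. The bootstrap resamples the same estimator, so it repairs the standard error and leaves the centre where it is.

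**Working it through.** **Inputs from the article.** Total-population SD 5.5 ("To detect a reduction of 0.7 score points (sd 5.5"); subgroup effect 1.5 and SD 3.8 ("we expect a reduction of 1.5 score points (sd 3.8) in the SDQ total difficulties score among the vulnerable sub group"); about 400 vulnerable pupils; cut at the 80th percentile.

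**Inputs assumed.** Normal scores; population SD 5.5 at every visit; correlation r between any two visits, 0.5 to 0.8; loss of 10 to 25% by 6 months; clustering ignored in the bias runs; two-sided alpha 0.05.

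**1. The plan's own figures.** n per group = 2(1.96 + 0.8416)² SD²/δ². For 3.8 and 1.5 this is 100.7, so 101 against the stated 102. For 5.5 and 0.7 it is 969.1, so 970 against 971. Both reproduce within rounding.

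**2. Effect of the cut on baseline.** z = 0.8416; λ = φ(z)/0.20 = 1.400; variance factor = 1 + zλ − λ² = 0.2186. Baseline SD in the subgroup = 5.5 × √0.2186 = 2.57.

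**3. Follow-up SD and correlations in the subgroup.** 6-month variance = 5.5² × (0.2186r² + 1 − r²). Baseline/6-month covariance = 5.5² × 0.2186r. 3-/6-month covariance = 5.5² × (r − 0.7814r²).

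| r | baseline SD | 6-month SD | corr. baseline–6 m | corr. 3–6 m |
|---|---|---|---|---|
| 0.5 | 2.57 | 4.93 | 0.26 | 0.38 |
| 0.6 | 2.57 | 4.66 | 0.33 | 0.44 |
| 0.734 | 2.57 | 4.19 | 0.45 | 0.54 |
| 0.8 | 2.57 | 3.89 | 0.53 | 0.60 |

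The value 0.734 makes the subgroup SD of change equal 3.8, which is one reading of the protocol's figure. Equal variances and equal correlations fail in every row.

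**4. Slope used for lost pupils.** Selection on baseline leaves the true slope of the 6-month score on baseline equal to r. Fitted by maximum likelihood, compound symmetry gives about 0.34 when r = 0.6 and about 0.44 when r = 0.734.

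**5. Bias by hand.** Let π be the proportion lost in an arm and d the baseline difference between lost and retained pupils. Using baseline and 6 months only, the error in that arm's 6-month mean is π(b − r)d, with b the fitted slope. Suppose 25% are lost in each arm, with d = 1.9 in the intervention arm and 0 in the control arm. At r = 0.734 the error is 0.25 × (0.44 − 0.734) × 1.9 = −0.14. With equal d in both arms, the two errors subtract to zero. Having 3-month scores for some of the lost pupils reduces the figure.

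**6. Bias by simulation.** Very large samples, true effect −1.5, all three visits, r = 0.6 or 0.734. Loss is logistic in the baseline or 3-month score, with log-odds slope 0.7 per SD.

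| Loss mechanism | Random intercept: bias | Unstructured: bias |
|---|---|---|
| Completely random | about 0 | about 0 |
| Same dependence in both arms, constant effect | at most 0.02 | at most 0.02 |
| Dependence in intervention arm only, 10–25% lost | −0.06 to −0.13 | within 0.02 |
| Opposite dependence by arm, 10–25% lost | −0.08 to −0.22 | within 0.02 |

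Milder dependence at about 10% loss gives about −0.05. The sign reverses if the dependence lies in the control arm.

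**7. Type I error.** Take SE = 0.45, from simulations of about 400 pupils. The rejection rate is Φ(−1.96 + bias/SE) + Φ(−1.96 − bias/SE): 5.1% at bias 0.05, 7.3% at 0.20 and 7.8% at 0.22.

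**8. Scale of the planned sensitivity shift.** With SD 3.8 and an assumed 20% loss, moving one arm's missing values by 0.2*SD moves its mean by 0.2 × 3.8 × 0.20 = 0.15 points, about the size of the bias above.

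**The case against.** The strongest reply is that the article does not state equal residual variances. A repeated-measures model with a pupil effect could carry visit-specific residuals, and an analysis plan that is not shown may say so. That is fair as far as it goes: the point holds for the model as written under its usual default. It is still not a complaint of silence, because the structure the article does name is a poor match for the primary population it defines.

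Second, the bias needs loss that depends on earlier scores differently by arm, and the article reports no such thing. Questionnaires are completed in school hours, absentees are given access and teachers receive two reminders, all of which should limit loss. This stands. On the other side, nobody is blinded and teachers organise completion, so differential loss is possible.

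Third, the 0.2*SD analyses probe errors of about this size. True, but they shift predictions from the same model, so they neither reveal nor correct its misfit.

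Fourth, the remedy was not tested in the full three-level model. About 400 vulnerable pupils in 191 teachers' classes is about 2 per class, and every bootstrap sample needs a refit. Convergence is therefore a real concern, and the fix must provide for it.

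A reader might infer that ordinary missing-at-random loss is enough to bias the primary result. It is not: with loss acting alike in both arms and a constant effect, the errors cancel.

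**Conclusion.** The point holds as a conditional, modest weakness with a cheap remedy. Under independent equal-variance residuals, the stated structure misfits the primary population by construction: baseline SD about 2.6 against about 3.9 to 4.9 at 6 months. The 6-month arm difference is unaffected with complete data, or when loss acts alike in both arms with a constant effect. If loss depends on earlier scores differently by arm, the bias is roughly 0.05 to 0.2 points, about 3 to 15% of the planned 1.5, and type I error is about 5 to 7.5% at an SE of 0.45. Its direction depends on which arm has the dependence, so nothing here says that the trial will favour the intervention.

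These sizes rest on normal scores, the assumed correlations, 10 to 25% loss and the chosen strength of dependence; none but the SD of 5.5 comes from the article. Harsher assumptions can be made to give about 0.3 points and 11% type I error, but the documents offer no basis for them.

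An effect that varies with baseline is a separate matter. With loss related to baseline, it gave a bias of about 0.06 to 0.13 of opposite sign under the random intercept. A covariance pooled over arms left most of that in place, so it is not counted as a gain from the change below.

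**What to change.** In Statistical methods, keep the school and teacher/class random effects. Replace the pupil random intercept by an unstructured 3×3 covariance over baseline, 3 and 6 months within pupil, estimated in the vulnerable subgroup for the primary analysis. Base the predictions in the four sensitivity analyses on that model.

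State a fallback in advance for non-convergence, including in bootstrap samples: at the least, a separate baseline variance and separate baseline/follow-up and 3-/6-month covariances.

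The cost is a sentence in the plan and a residual option in the Stata mixed model. There are six within-pupil covariance parameters instead of two, so four more. The SE rises by at most about 1 to 2% (0.465 to 0.469 and 0.440 to 0.450 in simulations of about 400 pupils without the school and class levels). If loss proves balanced, almost nothing has been given up.

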### Trial status

Randomisation of the schools and teacher training have been completed. Recruitment, data collection and teaching of the “.b” programme among the pupils began in September 2020.

## Discussion

This trial will estimate the effectiveness of a population-based strategy on mental health in Danish schoolchildren. Mental health includes well-being and functioning. The benefits of mindfulness training are universally for the entire spectrum of mental health [16]. Mindfulness is a resource that has the potential to enhance the ability to regulate emotions, behavior, well-being, and social competences. Thus, mindfulness training may promote mental health and prevent poor mental health in schoolchildren. However, implementation challenges exist regarding how to train school teachers adequately in order to become competent to teach mindfulness in schools. Based on experiences from the UK and Denmark, we have developed a school teacher training programme to teach the evidence-based mindfulness school programme “.b” in Danish schools and will estimate the effectiveness of this programme as a part of compulsory class room teaching, both among a vulnerable subgroup and among the total population.

The trial´s strengths include a well powered, rigorously effectiveness study design; a cluster RCT with 3 and 6-month follow-up data, including municipal and private schools across Denmark. The latter will enhance the external validity of the trial. The results of the trial will be of great relevance for decision-makers of mental health promotion and prevention programmes in adolescents in European countries. It is a strength that the “.b” teaching is embedded in the compulsory class room teaching making it possible to reach an entire population of school children without causing stigma to anyone. We use the same manualized “.b”-programme and school teacher training programme, currently being evaluated in a large scale trial in the UK [16]. An additional strength includes addressing implementation issues discovered in the UK [24] and adds support for implementation in our school teacher training programme. This added third part of our school teacher training programme is based on rigorous work of The Danish Association for Promoting Life Wisdom in Children”[30]. The first part of our school teacher training programme also differs to some extent from the teacher training route in the UK. The Danish school teachers participate in the evidence-based MBSR course, which is more intensive in both duration of sessions and home practice than the mindfulness programme used in the UK context [24]. MBSR is taught by MBSR teachers, who also take care of the the subsequent parts of the school teacher training programme. MBSR is delivered in groups consisting solely of school teachers in the project.

It is also an advantage that the pupils will complete the questionnaires during school hours, which may prevent drop-out of pupils in the analyses. However, it is a limitation that we only use self-reported outcome measures, and cannot exclude the possibility of information problems. It may be a disadvantage that we evaluate the effectiveness of “.b” based on the school teachers´ second delivery of the “.b” programme, as they have only had the opportunity to become familiar with the material once before in “real-life”. It cannot be ruled out that the school teachers´ mindfulness teaching competences and the effectiveness of the “.b”-programme may improve with more teaching experience [24]. It is also a limitation that we have not yet planned a more rigorous implementation evaluation. However, we plan to conduct post-hoc interviews among participating pupils and teachers on their experiences with the training.

In conclusion, this trial will in a rigorous cluster RCT design, estimate the effectiveness of a population-based strategy on mental health in Danish schoolchildren. It evaluates the effect of a school teacher training programme to teach the “.b” programme that takes into account implementation issues. “.b” will be taught as a part of compulsory class room teaching. Effectiveness will be evaluated both in a vulnerable subgroup and among the total population. The results may guide decision-makers of mental health promotion and prevention programmes in adolescents in European countries.

## Data Availability

The dataset will be available from the corresponding author by reasonable request after publication of planned articles.

## Abbreviations

SDQ: Strengths and Difficulties Questionnaire
WHO: World Health Organization
MBI: Mindfulness-based intervention
MBSR: Mindfulness-Based Stress Reduction
MBCT: Mindfulness-Based Cognitive Therapy
FOFBOC: Feet On Floor Bum On Chair
MISP: Mindfulness In Schools Project
WEMWBS: Warwick-Edinburgh Mental Wellbeing Scale
BRS: Brief Resilience Scale
DSWQ: School connectedness and bullying items from the Danish student well-being questionnaire
HRQoL: Health-related quality of life
CAMM: Child-Adolescent Mindfulness Measure
REDCap: Research Electronic Data Capture
